### Initiator analysis

We will apply a multinomial logistic model to estimate the probability of initiating SROM, methadone or buprenorphine/naloxone, incorporating selected baseline covariates, to adjust for confounding by indication at time zero. The treatment weights will be estimated by taking the inverse of the probability of initiating the observed form of OAT. The selection bias induced by censoring due to death or loss to follow-up will be controlled via censoring weights estimated from a pooled logistic regression model.^67^ To estimate weekly censoring weights, the model will incorporate an indicator for week (modelled with cubic splines), product of week and medication, and both time-fixed and time-varying covariates ().

$$SW_{it}=\prod_{j=1}^{t}\frac{\mathrm{Pr}.(C_{ij}=0|L_{i0},{\bar{C}}_{i,j-1}=0)}{\mathrm{Pr}.(C_{ij}=0|L_{i0},{\bar{L}}_{ij},{\bar{C}}_{i,j-1}=0)},$$

where $SW_{it}$ is the stabilized weight for the *i*th individual at time t, $C_{ij}$ is the censoring status for the *i*th individual at *j*th time, ${\bar{C}}_{ij}$ is the censoring history for the *i*th individual at *j*th time, $L_{i0}$ is the list of time-fixed covariates including treatment arm, ${\bar{L}}_{ij}$ is the time-dependent covariate history for the *i*th individual at *j*th time. Time-dependent covariates will be lagged by one week to ensure censoring is predicted using prior-week covariates. Same set of baseline and time-varying covariates will be included in the treatment and censoring models. Both treatment weights at time zero and censoring weights will be stabilized, truncated at the 99th percentile to limit the influence of extreme values and their product will be used as the final weights.[72] Covariate balance will be assessed using standardized mean differences (SMD), with SMD <0.10 considered balanced.[77] To fit the marginal structural model, a pooled weighted logistic regression model will be fitted to compare the time to OAT discontinuation, all-cause mortality, and overdose-related acute care visits across treatment groups. Based on the fitted models, individual time-to-event (survival) probabilities will be predicted weekly for each treatment arm by setting the treatment equal to a specific value (e.g., SROM, methadone, or buprenorphine/naloxone) for all individuals. These predicted probabilities will then be averaged across the population to get week-specific survival probabilities. The risk of the events will be estimated as one minus the averaged survival probability, with risk differences calculated for SROM initiators versus buprenorphine/naloxone and methadone. We will report hazard ratios, risk differences, and risk curves. Compatibility intervals and curves will be computed using the approach described in the Statistical analysis section.

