### Key measures

For sub-populations (i) to (viii), the primary exposure is the initiation of OAT with the dispensation of SROM, methadone and buprenorphine/naloxone in an initiator analysis framework. To compare the treatments at key dosing benchmarks, we will follow individuals receiving at least one dispensation of the following dosages per week. The key dosing benchmarks are aligned with BC clinical guidelines and previous literature:[6,58]

**Week 1:** SROM (≤240 mg), methadone (≤40 mg), and buprenorphine/naloxone (≤16 mg/4 mg).

**Weeks 2–3:** SROM (≥140 mg), methadone (≥30 mg), and buprenorphine/naloxone (≥12 mg/3 mg).

**Week 4 and beyond:** SROM (≥480 mg), methadone (≥80 mg), and buprenorphine/naloxone (≥16 mg/4 mg).

For sub-populations (ix) and (x), two treatment groups in per-protocol analysis framework will be defined as follows: individuals who switch to SROM within 30 days of initiating OAT with buprenorphine/naloxone or methadone, respectively, versus those who remain on their initial OAT type. Due to the lack of inpatient information on OAT dosing in our linked database, we will assume OAT receipt prior to hospitalization is continued daily throughout the duration of hospitalization.[6] Time to OAT discontinuation and all-cause mortality will be primary outcomes of interest for the initiator analysis. OAT discontinuation is defined as no OAT dispensation for ≥5 days for methadone and SROM, and ≥6 days for buprenorphine/naloxone. Additionally, time to overdose-related acute care visits (identified using ICD-10 codes T40, T42.4, and T43.6) will be assessed as a secondary outcome. The per-protocol analysis will assess the same set of outcomes: time to all-cause mortality, overdose-related acute care visits and OAT discontinuation.

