### Per-protocol analysis

We will conduct a per-protocol analysis to estimate treatment effects under sustained adherence at key dosing benchmarks, complementing the initiator effect.[86] To control the selection bias due to artificial censoring, we will consider two censoring models along with the propensity score models: (i) accounting for treatment switching, receipt of dose below key benchmark, and (ii) accounting for death, loss to follow-up, protocol violation by initiating pregnancy, dose taper, incarceration, or receipt of cancer or palliative care (see Table 3 for outcome specific censoring mechanism). Dose tapering is defined as two consecutive daily dose reductions without an intervening increase. Both censoring weights will be estimated using the approach described in the Initiator analysis section earlier. Final weights will be the product of the stabilized inverse probability of treatment weights at time zero and the post-baseline inverse probability of censoring weights, truncated at the 99th percentile. In the marginal structural model, we will apply a pooled logistic regression approach incorporating the final weights. The fitted model will be used to compute hazard ratios, risk differences, and risk curves. Compatibility intervals and curves will be computed using the approach described earlier. For sub-populations (ix) and (x), the censor-weighting approach will be similar, but we will apply a modified censoring mechanism as described in Table 3.

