Treatment switch		C_3_		C_3_		C_3_
The overdose-related first acute-care visit					outcome	outcome

a. end of study follow-up is either Dec 2022 or 24 months from time zero, whichever occurs earlier C_1_, C_2_, and C_3_ indicate different censoring mechanism: C_1_: censoring due to end of study follow-up; C_2_: censoring due to death (not the all-cause mortality outcome), loss to follow-up, deviation from the trial exclusion criteria such as initiation of pregnancy, incarceration, dose taper, cancer or palliative care, leaving out of BC. Dose taper will be defined as two consecutive daily dose decreases (without intervening increase); C_3_: censoring due to deviation from the dosing protocol as mentioned in the key measures section, including treatment switching. Censoring for violating dosing protocols will not be applied to the study sub-populations (ix) and (x), as defined in Table 2. For the clone designated for switching to SROM in these sub-populations, individuals will be censored at day 30 if they remain on the initial OAT beyond 30 days, but will not be censored if they switch to SROM within 30 days of initiation; Separate censoring models will be used for C_2_ and C_3_.

**Table 4. T4:** Time fixed and time-varying covariates to estimate the inverse probability of treatment and censoring weights

Variable	Category	How the variable is defined and measured
*Socio-demographic factors*		
Age	Continuous	Based on birth date information from the client registry.
Sex	Male/Female	Based on medical records that record sex.
Living in rural region	Yes/No	Based on the population of the assigned local health area[65]
Homelessness/unstable housing in past 5 years^‡^	Past year, Past 1–5 years, Never/>5 years	Defined through International Classification of Diseases (ICD) 10: Z59.0, Z59.1 from physician billing or hospital discharge records or 3 consecutive records of no fixed address from Social Development and Poverty Reduction (SDPR)
Incarcerated in past year^‡^	Yes/No	Admission to BC correctional facilities and identified through records in the past year from the provincial corrections database.
Receipt of income assistance in the past year^‡^	Yes/No	Identified through records in SDPR and PharmaCare plan information on medication dispensations, using records within the past year.
Calendar year of time zero	2010 to 2022	Determined based on the dispensation date from PharmaNet.
*Comorbidity*		

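### The per-protocol dose-censoring model is smooth in week, but the plan's dose benchmarks change in drug-specific steps at weeks 2 and 4, so the weights can underfit week-4 censoring

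*Protocol article*

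**What the plan says.** The Initiator analysis section specifies a pooled logistic model for weekly censoring by death or loss to follow-up. On time it says "the model will incorporate an indicator for week (modelled with cubic splines), product of week and medication", together with fixed and time-varying covariates. It adds: "Time-dependent covariates will be lagged by one week to ensure censoring is predicted using prior-week covariates". No number or position of knots is given. The text does not say whether the product uses linear week or the whole spline basis, and it names no covariate-by-time term.

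The Per-protocol analysis section then sets up two censoring models, the first "accounting for treatment switching, receipt of dose below key benchmark". It states: "Both censoring weights will be estimated using the approach described in the Initiator analysis section earlier". The footnote to Table 3 confirms "Separate censoring models will be used for C_2_ and C_3", and exempts sub-populations (ix) and (x) from dose censoring. The point therefore concerns (i) to (viii) only.

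The benchmarks that trigger C3 stand under Key measures: at least one dispensation per week at the stated dose.

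| Period | SROM | Methadone | Buprenorphine/naloxone (buprenorphine part) |
|---|---|---|---|
| Week 1 (ceiling) | 240 mg | 40 mg | 16 mg |
| Weeks 2-3 (floor) | 140 mg | 30 mg | 12 mg |
| Week 4 on (floor) | 480 mg | 80 mg | 16 mg |

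**The concern.** A smooth function of week suits death and loss to follow-up, which have no built-in change point. C3 does: the plan rewrites the rule at week 2 and again at week 4. Someone on an unchanged SROM dose of at least 140 mg but below 480 mg complies in week 3 and is censored in week 4. For buprenorphine/naloxone the corresponding gap is only 12 to 16 mg. The change is abrupt, falls at a known week and differs by drug.

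A spline over 104 weeks with few early knots spreads such a jump over neighbouring weeks. Week-4 weights are then too weak and later weights too strong, by different amounts in each arm. A single covariate coefficient must also serve both failing to reach a new floor and later lapses or switches. At stake is whether the per-protocol weights restore the censored population equally in the three arms. If they do not, a drug contrast can appear where none exists.

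**Working it through.** The plan gives no censoring rate, dose distribution or bias figure, so there is none of its own to reproduce.

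**1. Size of the steps (Key measures).**
- Weeks 2-3 floor to week-4 floor: SROM 480/140 = 3.43; methadone 80/30 = 2.67; buprenorphine/naloxone 16/12 = 1.33.
- Week-4 floor over week-1 ceiling: 480/240 = 2.0; 80/40 = 2.0; 16/16 = 1.0.
- The Table 1 footnote says SROM doses follow a 1:6 conversion from methadone. That gives 40 × 6 = 240, 30 × 6 = 180 and 80 × 6 = 480 mg, but weeks 2-3 state 140 mg. With 180 mg the SROM step would be 480/180 = 2.67, the same as methadone. The gap to buprenorphine/naloxone would remain.

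**2. How much an underfitted week loses.** Take a binary covariate L with odds ratio OR on C3, and p0, p1 the week-4 probabilities at L = 0 and L = 1, so p1 = p0·OR/(1 − p0 + p0·OR). The relative weight of L = 1 over L = 0 should be (1 − p0)/(1 − p1).
- True p0 = 0.5, OR = 3: p1 = 0.75, ratio 0.5/0.25 = 2.0. Fitted as p0 = 0.1: p1 = 0.25, ratio 0.9/0.75 = 1.2. Share of the log correction made: ln 1.2/ln 2.0 = 26%.
- OR = 1.5: needed ratio 1.25, obtained 1.05, share 22%.
- Fitted as p0 = 0.2 instead: shares of 43% (OR 1.5) and 49% (OR 3).

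**3. Exact population calculation under no drug effect.** Three arms, 104 weeks, one binary time-varying L, C3 fitted by pooled logistic regression, 99th-percentile truncation not applied. All inputs below are assumptions.

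Strongest inputs: week-4 C3 at L = 0 of 0.7/0.5/0.1 (SROM/methadone/buprenorphine-naloxone), OR 3, outcome HR for L of 4, L changing in 0.5% of weeks. True week-4 C3 is then 0.79/0.62/0.18 and true 24-month risk 9.1%.

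| Time terms in the C3 model | Fitted week-4 C3 | HR vs methadone | HR vs buprenorphine/naloxone |
|---|---|---|---|
| No weights | – | 0.99 | 0.91 |
| 4 knots (1, 8, 23, 69), linear product | 0.19/0.15/0.08 | 1.07 | 1.14 |
| 5 knots (1, 5, 14, 29, 69), spline product | 0.32/0.21/0.08 | 1.10 | 1.18 |
| Dense early knots (1-6, 20, 60), linear product | 0.63/0.56/0.39 | 1.05 | 1.09 |
| Dense early knots, spline product | 0.79/0.62/0.17 | 1.00 | 1.00 |
| Correct probabilities | 0.79/0.62/0.18 | 1.00 | 1.00 |

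Less extreme inputs (week-4 C3 from 55/45/10% down to 35/30/8%):
- Ordinary knots: SROM week-4 C3 of 0.29-0.63 is fitted as 0.07-0.16. HR versus buprenorphine/naloxone is 0.95-1.11, and versus methadone within about 4%.
- Dense early knots with a linear-week product: buprenorphine/naloxone C3 of 0.15 is fitted as 0.34; HR 0.94-1.11.
- Dense early knots with a full spline-by-medication product: HR 1.00 if the covariate effect is constant over weeks, 0.93-1.11 if it differs at week 4.

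The bias is nil when L does not predict C3 or when the jump is equal across drugs.

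**The case against.** The strongest reply is that the article fixes no knots. Their placement is commonly left to a full analysis plan, and its absence is no fault. On a weekly grid, early knots plus a full spline-by-medication product would follow the step and remove the bias when covariate effects are constant. That much stands. A reader might infer that the plan's model necessarily misses week 4, or that crossing the spline with medication never helps. Neither is supported: the second holds only for sparse knots. But early knots alone are not enough. If the product is one of linear week with medication, week-4 C3 is still misallocated between arms, and no covariate-by-phase term is named.

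It is also fair that floor ratios do not prove a spike. C3 depends on the doses people actually receive, one qualifying dispensation per week is enough, and C3 includes switching. Every bias figure is therefore assumption-based. Models with change-point terms recover the null partly because they share the time structure of the assumed data.

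Nor is week 2 a jump between floors: a ceiling gives way to a floor. And the SROM step of 3.43 rests on the 140 mg figure, which does not match the stated conversion.

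**Conclusion.** The point holds in conditional form. A time specification written for death and loss to follow-up is carried over to a censoring rule that the plan itself changes in drug-specific steps. With ordinary knots or a linear week-by-medication product, it can badly underfit week-4 C3.

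The consequence is possible residual selection bias in the per-protocol contrasts of (i) to (viii), mainly SROM versus buprenorphine/naloxone. Under the null the HR is about 0.95 to 1.10, up to 1.18 under the strongest inputs tried (risk differences there up to 1.4 points). SROM versus methadone moves little outside that extreme case, where it reaches 1.07 to 1.10 with ordinary knots. The direction is not predictable, because overweighting in later weeks can offset or exceed the underweighting at week 4.

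A reader might conclude that the SROM contrasts will be biased, or biased in a particular direction. The documents do not support that: it would need covariates that predict both C3 and outcome, unequal jumps between drugs, and censoring rates that are not given. The change is worth making because it is cheap and, according to Study status and timeline, no analyses have been run.

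**What to change.** - In the C3 model for (i) to (viii), add indicators for week 1, weeks 2-3 and week 4, crossed with medication, and use the spline from week 5. Equivalently, place knots at the change points and cross the full spline basis with medication.
- Where sample size permits, let the main time-varying covariates have a different effect in weeks 1-4 than later.
- Before fitting the outcome model, tabulate fitted against observed weekly C3 by arm.
- Keep the smooth spline for C2. The two models are already separate, so nothing else has to change.
- Reconcile the weeks 2-3 SROM benchmark under Key measures and in Table 1 (140 mg) with the 1:6 conversion in the Table 1 footnote (30 × 6 = 180 mg), because it sets the size of the SROM step.

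Cost: one diagnostic table and some extra parameters, which matter in small sub-populations. Table 4 has 25 covariate rows, so crossing every one with phase would add at least 25 coefficients to each C3 model. Limiting that term to the main time-varying covariates keeps it manageable.

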### Study follow-up

The time zero is the first dispensation date of methadone, buprenorphine/naloxone, or SROM. For initiator analysis, follow-up ends at the earliest of outcome, death, loss to follow-up, 24 months after time zero, or December 31, 2022. For per-protocol analysis, we will censor at additional events: (i) treatment switch or falls OAT dose below the key benchmark, and (ii) individuals initiate taper or violate eligibility criteria, such as being pregnant, or incarcerated, or had received cancer or palliative care (see Table 3).

However, for sub-populations (ix) and (x), where treatment is considered a time-varying exposure and individuals may be consistent with both treatment strategies up to 30 days of OAT episode, we will apply the ‘clone-censor-weight’ approach to emulate the per-protocol target trial.[59,60] In this approach, each individual will be replicated into two clones, one for each treatment strategy. When individuals are no longer consistent with the assigned strategy due to a treatment switch, taper initiation, or violation of eligibility, we will artificially censor the corresponding clone at that time. For the clone assigned to the switch to SROM group, individuals will remain uncensored if they switch to SROM within 30 days of OAT episode, and be censored at day 30 if they have not switched by then (see Table 3).

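### In the clone analyses of (ix) and (x), one censoring model shared by both arms cannot fit: predictors of switching raise C3 censoring in the stay clone and lower it in the switch clone

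*Protocol article*

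**What the plan says.** The Initiator analysis section describes "censoring weights estimated from a pooled logistic regression model" in which "the model will incorporate an indicator for week (modelled with cubic splines), product of week and medication, and both time-fixed and time-varying covariates". In the weight formula that follows, the baseline term "is the list of time-fixed covariates including treatment arm", so the arms share one model. The Per-protocol analysis section then states: "Both censoring weights will be estimated using the approach described in the Initiator analysis section earlier". For the two clone analyses it adds: "For sub-populations (ix) and (x), the censor-weighting approach will be similar, but we will apply a modified censoring mechanism as described in Table 3".

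The Study follow-up section says that "each individual will be replicated into two clones, one for each treatment strategy". A stay clone is artificially censored when the person switches. A clone assigned to switching will "be censored at day 30 if they have not switched by then".

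The Table 3 footnote divides the models by reason for censoring: "Separate censoring models will be used for C_2_ and C_3". C3 covers treatment switching and, outside (ix) and (x), the dosing benchmarks. Nothing divides the models by arm. The Statistical analysis section adds only that the artificial-censoring weights in (ix) and (x) condition on covariate history.

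**The concern.** After cloning, the two arms hold the same people, and what separates them is who gets censored. Table 2 itself expects early switching to follow poor response or poor tolerability. Such a marker raises the chance that the stay clone is censored and lowers the chance that the switch clone is. A model with a single coefficient for the marker cannot describe both.

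The weights must make the people left in each arm resemble everyone who entered. If they fail, poor responders stay over-represented in the switch arm. If poor responders also do worse, their prognosis is charged to SROM.

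No other planned analysis would reveal this. Table 1 gives (ix) and (x) only a per-protocol contrast, and Table 5 restricts the hdPS and instrumental-variable analyses to the initiator effect.

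**Working it through.** The plan states no figure on this point, so there is none to reproduce. The checks ask whether the weights return a zero effect when the true effect is zero.

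**Inputs from the plan:** two clones per person; stay clone censored at switching; switch clone censored at day 30 if not switched; weekly intervals; 24-month risk difference; model terms as quoted.

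**Assumptions, not in the plan:** one binary marker, prevalence 40% where fixed; odds ratio (OR) for switching and hazard ratio (HR) for the outcome of 1.5 to 3; baseline weekly hazard 0.004 unless stated; grace period of 4 weeks; later switching 0 or 0.3% per week.

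**Step 1, opposite signs.** Let 5% of marker-negative people switch by day 30, and let the OR be 3.
- Weekly switch probability without the marker: 1 − 0.95^(1/4) = 0.0127. With it: 0.0373.
- Stay clone: log-odds for censoring = ln 3 = +1.10.
- Switch clone: probability of censoring at day 30 = (1 − weekly probability)^4, which is 0.950 without and 0.859 with the marker. Log-odds = ln(0.859/0.141) − ln(0.950/0.050) = 1.81 − 2.94 = about −1.14.
- Overall switching: 0.6 × 0.050 + 0.4 × 0.141 = 0.086.

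**Step 2, the shared coefficient.** The pooled model was fitted with week-by-arm terms left free, which is more flexible than splines, and one marker coefficient. For this scenario the coefficient is +0.03 with no later switching and +0.68 with later switching. For overall 30-day switching of 3.5% to 54%, the ranges are +0.02 to +0.20 and +0.31 to +0.88.

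**Step 3, effect on the switch-arm weights.** Ignoring the few events before day 30, uncensored marker-positive clones need 0.050/0.141 = 0.35 times the weight of marker-negative ones.
- A coefficient of +0.03 gives a ratio of about 1.03, which is almost no adjustment.
- A coefficient of +0.68 multiplies the odds of staying uncensored by e^(−0.68) = 0.51. The fitted probabilities are then 0.106 and 0.057 (check: 0.6 × 0.106 + 0.4 × 0.057 = 0.086). The ratio is 0.106/0.057 = about 1.9, which is the wrong direction.

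**Step 4, risk difference at 24 months with a fixed marker** (switch minus stay, percentage points; truth 0; no truncation of weights; marker not in the outcome model):

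| Scenario | No weights | Model as written | Arm-specific |
|---|---|---|---|
| OR 3, HR 3, no later switching | +9.9 to +12.2 | +10.0 to +12.1 | 0.0 |
| OR 3, HR 3, later switching | +12.1 to +13.7 | +13.4 to +16.0 | 0.0 |
| OR 2, HR 2, both | +3.9 to +4.9 | +3.9 to +6.2 | 0.0 |
| OR 1.5, HR 1.5, both | +1.2 to +1.5 | +1.3 to +2.0 | 0.0 |
| OR 3, HR 3, both, weekly hazard 0.0005 (24-month risk 8.8%) | +2.5 to +3.3 | +2.6 to +3.8 | 0.0 |

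These figures show the mechanism. They are not the bias of the plan, because a baseline marker could be handled in the outcome model. With a fixed marker placed there and standardised over, the risk difference was 0.000 without any weights in four scenarios (OR 2 to 4.5, HR 2 to 3), against +4.4 to +13.7 points without the covariate.

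**Step 5, a marker that can arise after baseline.** This is the case that only the weights can handle. Two separate calculations were made under a true null.
- First: log-odds for censoring of +0.41 to +1.11 (stay), −0.35 to −1.00 (switch) and +0.03 to +0.57 (pooled). Risk difference: +0.7 to +8.6 points unweighted, +0.7 to +9.4 with pooled weights, and about 0 with arm-specific or grace-interval weights.
- Second: +0.7 to +8.3 unweighted and +0.7 to +8.1 with pooled weights. Depending on the scenario, the pooled weights removed at best about 22% of the bias and at worst added about 16%. Arm-specific models that kept the stabilised formula of the Initiator analysis section left +0.3 to +3.2. The grace-interval weight set out under the fix gave −0.1 to 0.0.

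**The case against.** The strongest reply is that the quoted model is written for death and loss to follow-up in the initiator analysis. For (ix) and (x) the plan says similar, not identical. Everyone in each of these sub-populations starts on the same drug, so the week-by-medication product cannot carry over literally and some adaptation is implied. A condensed article may leave its form to a fuller plan. This stands as a reason for caution about intent. It does not remove the point: arm is named as a covariate, the only stated change is to the censoring mechanism, and models are separated by reason only. An analyst following the text would fit the shared model.

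Several stronger readings are tempting, but the documents do not support them.
- **The weights are the only confounding control.** This is not established for baseline covariates. The stabilising numerator conditions on them, and the averaging of predicted survival would fit an outcome model that contains them. The claim holds for post-baseline confounders.
- **The two effects cancel.** They nearly do so only when switching is confined to the first 30 days. With later switching, the shared coefficient takes the stay-arm sign.
- **The same defect affects (i) to (viii).** Nothing there forces a sign reversal, and no calculation shows harm. Models by drug would be a modelling preference.
- **A cubic spline cannot follow the day-30 jump.** No knots are given and this was not tested. The problem appears even with week-by-arm terms left free.
- **A single size for the bias.** Every figure rests on assumed values, and the fixed-marker calculation omits the planned truncation at the 99th percentile.

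**Conclusion.** The point holds for the C3 artificial-censoring model in (ix) and (x). The opposite signs follow from the design and need no assumed values. Followed as written, the plan leaves most or all post-baseline confounding of switching in the estimate, and in some scenarios adds to it.

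The size does depend on assumptions: about +0.7 to +9 percentage points at 24 months under a true null, for switching ORs and outcome HRs of 1.5 to 3 and a weekly hazard of 0.004. The sign presumes a marker that raises both switching and risk; the bias then makes switching to SROM look harmful. The change should be made before analysis, which according to the Study status and timeline section has not begun.

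**What to change.** In the Per-protocol analysis section and the Table 3 footnote, state for (ix) and (x) that the C3 model is fitted separately by clone strategy:
- **Stay clone:** model the weekly hazard of switching given covariate history.
- **Switch clone:** set the C3 factor to 1 before the last grace interval. In that interval, weight those who switch by the inverse of their modelled probability of switching, given covariate history and not having switched earlier. Leave earlier switchers at factor 1, and apply no C3 factor afterwards.

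The grace-interval rule should be written out, because adding only that models are fitted by arm may not be enough. People who switch in the last interval must stand in for everyone who reached it unswitched, and a stabilised factor pulls their weight back towards 1. The second calculation in step 5 shows the bias that this left.

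No change to the C2 models, or to the models for (i) to (viii), is needed on this ground. The cost is a few sentences, a modest change in code, and slightly less stable coefficients in the smaller arm.
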